### 4.3 Inclusion and exclusion criteria:

#### **Inclusion criteria**

1. Diagnosis of T2DM in the electronic medical record of private health insurance companies (HbA1c reading 7% or higher; age  $\geq 18$  years).
2. Willingness to receive phone calls and messages for monitoring the disease and for tele-education.
3. Willingness to use the standard monitoring devices (glucometer), synchronized with the telemonitoring system according to the study protocol throughout the 12-month study period.

#### **Exclusion criteria**

1. Cognitive impairment based on a diagnosis of dementia or mild cognitive impairment reported in the medical records.
2. Self-declared reluctance to receive phone calls or messages for disease management.
3. Pre-existing condition: chronic kidney disease stage 5; patients with any end-stage disease with a life prognosis of fewer than two years; or pregnant women.

### 4.4 Recruitment plan and Process for obtaining consent:

The team members of private health insurance companies partnered with the Klivo startup will pre-screen patients diagnosed with T2DM. After this stage, the eligibility criteria will be used. Patients meeting the eligibility criteria will be contacted by a Klivo team member via a phone call, during which they will be asked for verbal authorization to share their data for statistical analysis. Participants will be dismissed from signing a written free informed consent, but the terms of the free informed consent will be read to them during the phone call, before the start of the research, and a written copy of the terms will be sent to them.

### 4.5 Study setting, data collection timeframe:

Klivo is a Brazilian startup founded in 2020 and certified by the Brazilian Society of Diabetes in September 2021. KIP seeks to follow up individuals with chronic conditions in their selfcare along time. Its main partners are health insurance companies in Brazil. The Klivo team supports individuals in obtaining consistent results in metabolic conditions and improving their quality of life. This digital platform will facilitate data collection related to an individual's health, analyze data to evaluate clinical or pre-clinical conditions, and will provide personalized management of the individual's journey along 12 months.

### 4.6 Source of research material and Research development phases:

This is a prospective, observational, and transversal study that will analyze data from a database of a partner startup (Klivo), which follows up patients with diabetes mellitus through a digital platform. The authors of this research will receive encrypted data, while the participants' identity will remain totally anonymous.

The protocol developed and operated by the startup Klivo is detailed below:

The private health insurance team members will pre-screen patients diagnosed with T2DM for eligibility as described below and advise a Klivo team member to approach the identified patients for registration in KIP. The adopted eligibility criteria are as follows.

The team members of private health insurance companies partnered with the Klivo startup will pre-screen patients diagnosed with T2DM. After this stage, the eligibility criteria will be used. Patients meeting the eligibility criteria will be contacted by a Klivo team member via a phone call, during which they will be asked for verbal authorization to share their data for statistical analysis. Participants will be dismissed from signing a written free informed consent, but the terms of the free informed consent will be read to them during the phone call, before the start of the research, and a written copy of the term will be sent to them. Next, the team will remotely apply standardized questionnaires via phone calls, to record the participants' demographic, clinical, and laboratorial data. For 12 months, nurses will remotely supervise participants through a management process. This method is an intensive lifestyle intervention program adapted from the National Standards for Diabetes Self-Management Education and Support [11]. Via a phone call, the team will adopt a standardized questionnaire (The International Consortium for Health Outcomes Measurement [12]) to record data about the participants' demographic characteristics, medical history, and environmental risk factors. Blood pressure and anthropometric parameters will be based on self-reported values obtained during the phone call. Blood glucose, HbA1c, total cholesterol, triglycerides, and lipoprotein fractions as high-density lipoprotein (HDL-c) and low-density lipoprotein (LDL-c) will be measured by standard techniques in the participants' usual laboratory, after fasting for at least eight hours, every three months. The scales Morisky Green [13], PAID [14], WHO-5 [15], and PHQ-9 [16] will also be applied. The program will include tele-education via weekly phone calls over six weeks in one-on-one orientation sessions (1. Introduction. Questionnaires. One-on-one orientation about hypoglycemia. 2. Questionnaires. Problem-solving skills and IDEA approach (Identify the problem, Define possible solutions, Evaluate the solutions, Act on the best solution). Definition of an individualized plan for the subsequent interventional sessions. 3. Nutrition and physical activity. 4. Medications and relation between administration time and meals. 5. Emotional health, smoking, and alcohol. 6. Importance of healthy habits and glucose control in the long term. Participants that require insulin therapy will have an additional session about administering the injection. Besides traditional interfaces (phone calls, e-mails, text messages, and the Web), KIP will include smartphone applications and wearable devices (klivo.com). Participants will use standardized Bluetooth-enabled devices to transmit their capillary glucose. When abnormal glucose levels are detected, the participant and their medical doctors will be contacted via a phone call (capillary glucose < 54 mg/dL or > 450 mg/dL) or text message (capillary glucose between 55 and 70 g/dL or 350 and 449 mg/dL). The participant will be monitored every 15 minutes to guarantee that hypo or hyperglycemia is reverted. If specific needs are detected, nurses will suggest additional scheduled phone calls with a multidisciplinary team (psychologists, nutritionists, and physical educators). If the participant presents  $\geq 3$  episodes of hypoglycemia, their medical doctor will receive an e-mail with a report about the participant's glycemic control. Collected information will be encrypted, stored, and kept confidential for exclusive use of the Klivo Research Center. In case of distribution to team members or third parties for the purpose of statistical analyses, participants' data will be de-identified to ensure privacy.

Besides traditional interfaces (phone calls, e-mails, text messages, and the Web), Klivo will include smartphone applications and wearable devices (klivo.com). However, telemonitoring

will still be needed, mainly for the elderly population [17]. Participants will use standardized Bluetooth-enabled devices to transmit their capillary glucose.

#### 4.7 Protective measures or minimization of any risks for the participants

The program involves educational action in health and monitoring (mainly glucose level control).

Concerning the risks associated with disease diagnosis (for example, hypo or hyperglycemia), measures will be taken to mitigate such events. A phone call will be made, or a text message will be sent if abnormal glucose parameters are detected. Phone calls will be made if capillary glucose is < 54 mg/dL or > 450 mg/dL, and text messages will be sent if capillary glucose is between 55 and 70 g/dL or 350 and 449 mg/dL. The participant will be monitored every 15 minutes to guarantee that hypo or hyperglycemia is reverted.

If specific needs are detected, nurses will suggest additional scheduled phone calls with a multidisciplinary team (psychologists, nutritionists, and physical educators).

If the participant presents three or more episodes of hypoglycemia, their medical doctor will receive an e-mail with a report about the participant's glycemic control.

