### **Methods**

The Klivo Intervention Program is an intensive lifestyle intervention method that seeks to improve the daily lifestyle of adults with type 2 diabetes mellitus, aged  $\geq 18$  years, with glycated hemoglobin (HbA1c) of 7% or higher. The program is free for patients that are users of partner health plans and healthcare provider organizations. HbA1c and time in target blood glucose range will be evaluated at baseline and stipulated time points. The program will be based on a 12-month management process during which participants will be remotely supervised by nurses every fifteen days. When abnormal glucose levels are detected, the participant and their medical doctor will be contacted according to an established protocol. Clinical and laboratory data, weight control, quality of life, mental health, medication adherence, confidence in self-management, healthcare utilization, diabetic literacy and related distress will be evaluated through validated electronic questionnaires. The program will include tele-education via phone calls along the first six weeks. The laboratorial data and data reported over the phone will be assessed at baseline and 3, 6, 9, and 12 months after intervention; the questionnaires will be applied in the first and last months.

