##### **Monitoring**

Nurses will make phone calls to the participants every fifteen days over twelve months to support ongoing self-management of T2DM. All participants will continue to receive treatment from their regular medical doctors during the 12-month time.

Moreover, depending on the seriousness of the situation, a phone call will be made, or a text message will be sent to the participants if abnormal parameters are detected. Phone calls will be made if capillary glucose is  $< 54$  mg/dL or  $> 450$  mg/dL, and text messages will be sent if capillary glucose is between 55 and 70 g/dL or 350 and 449 mg/dL. The participants will be monitored every 15 minutes to guarantee that hypo or hyperglycemia is reverted.

If specific needs are detected, nurses will suggest additional scheduled phone calls with a multidisciplinary team including psychologists, nutritionists, and physical educators.

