## **6. RISKS AND BENEFITS**

6.1 Risks: The program involves educational actions in health and monitoring (especially glycemic control). Risks are related to disease diagnosis (for example, hypo or hyperglycemia) and measures to mitigate such events. There are also risks involved with data handling (leak, hacker attack, risks to safety and privacy, for instance).

6.2 Paying for participants' expenses regarding the research:  
Not applicable

6.3 Benefits:

Participants will receive information about the primary pathology (diabetes mellitus) and associated factors. Instant alerts will be sent to participant when abnormal glucose levels are detected.

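### The glucose alert rule assigns neither a call nor a text at exactly 54 and 450 mg/dL, and prints the low text band in g/dL

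*Protocol*

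**What the plan says.** The alert rule appears three times in the protocol, each time with the same numbers.

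- Section 4.7, on protective measures: "Phone calls will be made if capillary glucose is < 54 mg/dL or > 450 mg/dL", followed by "text messages will be sent if capillary glucose is between 55 and 70 g/dL or 350 and 449 mg/dL".
- Section 4.6, in the program description, in compressed form: "capillary glucose < 54 mg/dL or > 450 mg/dL) or text message (capillary glucose between 55 and 70 g/dL or 350 and 449 mg/dL".
- Section 4.8, under Monitoring, which repeats the section 4.7 limits and adds that the choice between call and text depends on how serious the situation is.

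Two more general statements surround the rule. The Methods part of the abstract says "When abnormal glucose levels are detected, the participant and their medical doctor will be contacted according to an established protocol". Section 4.7 says "A phone call will be made, or a text message will be sent if abnormal glucose parameters are detected". All three statements of the rule are also followed by monitoring every 15 minutes until the abnormal value has been reversed.

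**The concern.** A two-level alert rule should give every reading in the alert range exactly one response. Here the call limits exclude their own end points (below 54, above 450), and the text bands stop one unit short of them (from 55, up to 449). The values 54 and 450 therefore fall between the two levels, at the points where the response should change from the milder to the more urgent one.

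The low text band also carries a unit that cannot be right for blood glucose.

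What is at stake is participant safety. Taken literally, the rule does not tell staff whether a hypoglycemia reading of 54 mg/dL calls for a phone call or a text message, and the same holds at 450 mg/dL. The section that contains it is the one meant to show how risk to participants is reduced.

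**Working it through.** **Inputs** (sections 4.6, 4.7 and 4.8 Monitoring, identical in all three)

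- Call: x < 54 or x > 450.
- Text: x between 55 and 70, or between 350 and 449.
- Assumptions: g/dL is read as mg/dL, between includes its end points, and the meter reports whole mg/dL.

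The protocol gives no derived figure to reproduce, so the check is to classify every whole-number reading from 20 to 600 mg/dL. The alert ranges are 70 or below and 350 or above. Readings of 71 to 349 are outside the rule.

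**Printed rule**

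| Range | Call | Text | Neither | Total |
|---|---|---|---|---|
| 20 to 70 | 20–53: 34 values | 55–70: 16 values | 54: 1 value | 34 + 16 + 1 = 51 |
| 350 to 600 | 451–600: 150 values | 350–449: 100 values | 450: 1 value | 150 + 100 + 1 = 251 |

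The unassigned set is {54, 450}.

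**Sensitivity to the assumptions**

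- If between excludes its end points, the unassigned set grows to {54, 55, 70, 350, 449, 450}. The inclusive reading is the more natural one and the kinder to the protocol.
- If the meter reported fractions, each gap would become an interval: 54 ≤ x < 55 and 449 < x ≤ 450. The protocol does not give the meter's resolution.

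**Unit**

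1 g/dL = 1,000 mg/dL, so 55 to 70 g/dL is 55 × 1,000 = 55,000 to 70 × 1,000 = 70,000 mg/dL. That is not a possible blood glucose. Every other limit in the rule is in mg/dL, so mg/dL is clearly meant.

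**Two possible repairs**

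- A: call at x ≤ 54 or x ≥ 450, text bands unchanged. Low range: 35 calls + 16 texts = 51. High range: 151 calls + 100 texts = 251. Nothing is unassigned, and 54 and 450 both become calls.
- B: call limits unchanged, text at 54–70 or 350–450. Low range: 34 calls + 17 texts = 51. High range: 150 calls + 101 texts = 251. Nothing is unassigned, and 54 and 450 both become texts.

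Each repair changes the response at those two values and nowhere else.

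**The case against.** The strongest reply is that nothing of consequence is left open. Contact on an abnormal reading is promised in general terms in the abstract and in section 4.7. The Monitoring text gives seriousness as the guide to the channel, and the 15-minute monitoring is not tied to either channel. Nurses also call every fifteen days, and the doctor receives an e-mail after three or more hypoglycemia episodes. The startup runs the platform under its own procedure, so the protocol only describes a rule whose working settings lie elsewhere. The unit is a typing or translation slip that nobody could act on literally.

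Most of this stands, and it keeps the point minor. The unit slip has no practical effect beyond needing correction. A reader might infer that a participant at 54 or 450 mg/dL would get no response at all, or that alerts have been missed. The document supports neither: the general duty of contact remains, the deployed thresholds are not shown, and the frequency of such readings is not given. What the reply does not do is say which response applies at the two values. The fixed numbers are meant to answer that, and no section does.

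A reader might also infer that the protocol contradicts itself on who is alerted. Section 4.6 says "the participant and their medical doctors will be contacted via a phone call", while section 4.8 says "a phone call will be made, or a text message will be sent to the participants if abnormal parameters are detected" and section 6.3 says "Instant alerts will be sent to participant when abnormal glucose levels are detected". This does not hold up. The abstract and section 4.6 agree on participant and doctor, and no section excludes the doctor. In section 4.8 the mention of participants can belong to the text message alone. Section 6.3 lists benefits to participants and is not an operating rule. The three-episode e-mail is a separate step.

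**Conclusion.** Wrong as written, minor. With inclusive bands and whole mg/dL readings, exactly two values in the alert ranges, 54 and 450 mg/dL, have neither a call nor a text assigned in any of the three statements of the rule. The low text band is misprinted in g/dL in all three.

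The finding is confined to participant safety at those two values, and there only to which response is due. It says nothing about how the platform actually behaves. It does not touch HbA1c, time in range or the statistical analysis, and it should not be read as a defect in the study's inference.

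**What to change.** In sections 4.6, 4.7 and 4.8 (Monitoring), state:

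- phone call at ≤ 54 mg/dL or ≥ 450 mg/dL;
- text message at 55 to 70 mg/dL or 350 to 449 mg/dL, end points included.

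This is repair A, the safer of the two because both boundary readings get the more urgent response. Repair B also closes the gaps, if there is a clinical reason to keep the printed call limits. If the meter reports fractions, write the text bands as above 54 up to 70 and from 350 to below 450, so that no interval is left open.

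Then check the thresholds set in the platform against the corrected text. The cost is two inequality signs and one unit in each of three places, plus that check. Nothing in data collection or analysis changes.

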#### 4.8 Detailed description of the data collection instrument

##### **These activities will be performed by the partner startup (Klivo):**

The intervention will begin with one 60-minute one-on-one orientation session about the program. The diabetes educator will call the participant at the previously scheduled time.

KIP will include tele-education via weekly phone calls over six weeks in one-on-one sessions about hypoglycemia, nutrition, physical activity, lifestyle, mental health, and regular use of medication as described below.

##### **Sessions**

1. Introduction. Questionnaires. One-on-one orientation about hypoglycemia.
2. Questionnaires. Problem-solving skills and IDEA approach (Identify the problem, Define possible solutions, Evaluate the solutions, Act on the best solution). Definition of an individualized plan for the subsequent interventional sessions.
3. One-on-one orientation about nutrition and physical activity.
4. One-on-one orientation about medications, especially about the relation between insulin administration time and meals.
5. One-on-one orientation about emotional health, smoking, and alcohol.
6. One-on-one orientation about healthy changes and glucose control in the long term.

Participants that require insulin therapy will take one more orientation session about administering the injection.

##### **Monitoring**

Nurses will make phone calls to the participants every fifteen days over twelve months to support ongoing self-management of T2DM. All participants will continue to receive treatment from their regular medical doctors during the 12-month time.

Moreover, depending on the seriousness of the situation, a phone call will be made, or a text message will be sent to the participants if abnormal parameters are detected. Phone calls will be made if capillary glucose is  $< 54$  mg/dL or  $> 450$  mg/dL, and text messages will be sent if capillary glucose is between 55 and 70 g/dL or 350 and 449 mg/dL. The participants will be monitored every 15 minutes to guarantee that hypo or hyperglycemia is reverted.

If specific needs are detected, nurses will suggest additional scheduled phone calls with a multidisciplinary team including psychologists, nutritionists, and physical educators.

### **Contacting medical doctors**

If the participant presents three or more episodes of hypoglycemia, their medical doctor will receive an e-mail with an alert about their glycemic control.

### **Clinical and laboratorial measurements**

#### **Questionnaires**

To obtain information related to the participants' demographic characteristics, medical history, and environmental risk factors, participants will answer questions during a phone call when the nurse will fill in an electronic questionnaire designed according to the ICHOM criteria [12]. Additionally, information about physical activity (time per week), smoking status, and alcohol consumption (amount and frequency per week) will be collected according to the ICHOM criteria [12].

To verify medication adherence, data will be collected via a standardized instrument called the Morisky Green scale [13]. The relationship between participants and T2DM will be evaluated by the Problem Areas in Diabetes (PAID) questionnaire [14]. The WHO Well-Being Index (WHO-5) instrument will be used to assess psychological well-being [15]. The depression status will be estimated by the Patient Health Questionnaire (PHQ-9) [16], and strategic directions will be suggested according to the score.

#### **Blood pressure measurement**

Systolic and diastolic blood pressures will be based on values reported by the participant during telephonic contact (self-reported).

#### **Anthropometric parameters**

Participants will report all the anthropometric parameters during telephonic contact. To measure waist circumference (WC), participants will be instructed to place a tape measure around their body, at the top of the hipbone, which is usually at the level of the umbilicus. Increased WC is defined as  $\geq 88$  cm for women and  $\geq 102$  cm for men.

Body mass index (BMI) will be calculated as the body weight (kg) divided by the squared height ( $m^2$ ). Overweight will be defined as  $BMI \geq 25$   $kg/m^2$  and  $< 30$   $kg/m^2$ , and obesity will be defined as  $BMI \geq 30$   $kg/m^2$ .

#### **Biochemical analysis**

Blood glucose, HbA1c, total cholesterol, triglycerides, and lipoprotein fractions as high-density lipoprotein (HDL-c) and low-density lipoprotein (LDL-c) will be measured by standard techniques in the participants' usual laboratory, after fasting for at least eight hours, every three months.

#### **Disease diagnosis**

Systolic blood pressure (SBP)  $\geq 140$  mmHg or diastolic blood pressure (DBP)  $\geq 90$  mmHg (measured in the doctor's office or at home) or antihypertensive drug use will be used for hypertension diagnosis [18]. T2DM will be defined by the presence of fasting glucose  $\geq 126$  mg/dL or antidiabetic drug use. Dyslipidemia will be defined by drug use.

#### 4.9 Statistical analysis

**These activities will be performed by the investigator [name]. [name] and her advisee:**

Analyses will be conducted by comparing pre- and post-intervention parameters of the patients selected for KIP.

For all the measurements, clinical and laboratorial characteristics will be assessed by descriptive statistics. Categorical variables will be expressed as percentages, and continuous variables will be expressed as mean  $\pm$  SD or median (interquartile range). The Kolmogorov-Smirnov test will be used to check data normality. The characteristics of the participants in the different groups (defined according to clinical characteristics) will be evaluated by t-test or Wilcoxon rank test (continuous variables) or Pearson's chi-squared test (categorical variables). Logistic regression will be used to assess the association between independent variables and diabetes mellitus. The analyses will be adjusted for age and sex. Receiver Operational Characteristics (ROC) curves will be performed to evaluate the performance of the suggested models and models that are scientifically sound, and the area under the curve (AUC) will be used to measure the discriminatory power of the identified explanatory variables for T2DM. Statistical analysis will be performed by using RStudio software version 1.3.1093. The significance level will be set at 5%.

Sub-groups (e.g., group I and group II) will be created on the basis of pre-existing conditions described as follows:

Group I: Participants with no or only mild non-proliferative diabetic retinopathy without any macular involvement; chronic kidney disease up to stage 3a (eGFR  $\geq 45$  mL/min/1.73 m^2); participants with no known macrovascular diseases.

Group II: Participants with retinal pathologies documented in the medical records, including proliferative diabetic retinopathy (moderate to severe) or other retinal or macular diseases; or chronic kidney disease stage 3b or 4; or known peripheral vascular, coronary, or cerebrovascular disease.

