## **2. OBJECTIVES**

### **2.1 Main objective:**

This study will evaluate the self-reported clinical and laboratorial aspects of patients with T2DM recruited for the KIP cohort. Additionally, mental health, medication adherence, confidence in self-management, healthcare utilization, diabetic literacy, and related distress will be evaluated by using validated questionnaires. Two primary outcomes will be evaluated: glycated hemoglobin (HbA1c) and time in range (TIR), defined by the percentage of time an individual remains with blood glucose levels in a target range of 70 to 180 mg/dL.

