### **2.2 Specific objectives:**

1. To compare the participant's HbA1c values at baseline and 3, 6, 9, and 12 months after inclusion in KIP.
2. To identify the percentage of time in range (TIR) and, hence, the number of severe hypoglycemic events over 12 months.

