### **3. RESEARCH HYPOTHESES**

#### **3.1 Main hypothesis:**

KIP participants should present improved HbA1c and TIR along the intervention as compared to baseline values.

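### The primary question is within-patient change, but section 4.9 gives it no within-patient method and no primary visit, and section 4.2 limits the comparison to completers

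*Protocol*

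**What the plan says.** **The question.** Section 2.1 states: "Two primary outcomes will be evaluated: glycated hemoglobin (HbA1c) and time in range (TIR"). Section 2.2 sets the first specific objective: "To compare the participant's HbA1c values at baseline and 3, 6, 9, and 12 months after inclusion in KIP". For TIR, section 2.2 speaks only of the percentage over 12 months. The main hypothesis in section 3.1 is: "KIP participants should present improved HbA1c and TIR along the intervention as compared to baseline values".

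**The analysis.** Section 4.9 opens with: "Analyses will be conducted by comparing pre- and post-intervention parameters of the patients selected for KIP". No test or model is attached to that sentence. The methods it then names are:

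- Continuous characteristics "will be evaluated by t-test or Wilcoxon rank test (continuous variables") and categorical ones by Pearson's chi-squared test. The sentence assigns both to comparisons between groups defined by clinical characteristics, and the section goes on to define Groups I and II.
- Logistic regression, ROC curves and AUC, with type 2 diabetes as the outcome.
- A normality check: "The Kolmogorov-Smirnov test will be used to check data normality".
- A single 5% significance level, with no primary visit and no rule for two primary outcomes.

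**The analysed cohort.** Section 4.2 takes all patients enrolled in the programme, except those who refuse to share data or are lost to follow-up. The target is at least 100. No SD, effect size, correlation, power or dropout rate is given.

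**The concern.** The statistics section is specific about tests, software and significance level, yet none of the inferential methods it lists answers the primary question. The group tests compare different people. The regression and ROC analyses model a diagnosis that section 4.3 makes a condition of entry, so it does not vary in this cohort. Three things are at stake.

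1. The analyst must choose the primary method without guidance from the protocol, possibly after seeing the data.
2. HbA1c is compared with baseline at four visits at a flat 5%, and no visit is named as the one that counts. Improvement could be claimed on whichever visit reaches significance.
3. Removing patients lost to follow-up makes the comparison one of completers. If people whose HbA1c worsens are more likely to leave, those who remain look improved even when nothing has changed.

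**Working it through.** The protocol states no figure for this comparison beyond the recruitment target, which has no derivation, so there is nothing to reproduce.

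**Inputs from the protocol**
- N = 100 (section 4.2); level 5% (section 4.9; two-sided assumed, since sidedness is not stated).
- Five HbA1c visits, hence four changes from baseline (section 2.2).
- Two primary outcomes (section 2.1).

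**Inputs assumed**
- HbA1c SD 1.5 points; within-patient correlation r = 0.3 to 0.7; true fall of 0.4 points for the power figures; dropout 0 to 30%.

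**Step 1: which method answers which question**

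| Method in section 4.9 | Stated target | Addresses change in HbA1c or TIR? |
|---|---|---|
| t-test, Wilcoxon, chi-squared | Clinical groups | No |
| Logistic regression, ROC/AUC | Type 2 diabetes | No |
| Pre/post comparison | Participants before and after | Yes, but no method attached |

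**Step 2: false-positive risk with no primary visit**
- Four independent tests: 1 − 0.95^4 = 0.185.
- The four changes share one baseline, so they are correlated. Simulated paired t-tests (20,000 runs, N = 100, r = 0.3, 0.5, 0.7) give 15–16%, or about 16%. This is roughly three times the nominal 5% for HbA1c alone.
- If TIR were also tested at all four visits: 1 − 0.95^8 = 0.337 if independent; 25–29% simulated with cross-outcome correlation 0 to 0.7. This is conditional, because the protocol does not fix four TIR tests.
- With one visit per outcome and no sharing rule: up to 1 − 0.95^2 = 0.0975 if the outcomes are independent. Naming a visit therefore does not settle the matter of two primary outcomes.

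**Step 3: completers only**

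Simulation with no true change, N = 100, SD 1.5 and equal correlation between visits. The chance of leaving before months 6, 9 and 12 rises with the change from baseline seen at the previous visit (logit = −2.7 + 1.0 × change).

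| r | Dropout | Mean change, completers | Type I error, paired t on completers | Mean change, likelihood model on all |
|---|---|---|---|---|
| 0.5 | 30% | −0.28 | 38% | 0.00 |
| 0.7 | 25% | −0.17 | 24% | 0.00 |

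The model recovers the truth here because dropout depends only on observed values (missing at random).

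**Step 4: what the model gains in power**

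SD of change = 1.5 × √(2(1 − r)), which is 1.77, 1.50 and 1.16 at r = 0.3, 0.5 and 0.7. For a fall of 0.4, N = 100 and complete data, paired-t power is 0.61, 0.75 and 0.93. The month-12 contrast from the repeated-measures model has the same precision (variance ratio 1.00). With 20–30% dropout the variance ratio of completers to model is 1.07 to 1.19, a gain of about 2 to 7 power points (for example 0.868 to 0.888, or 0.598 to 0.667).

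**The case against.** **This is omission, and an unseen SAP may fill it.** Model, covariance structure and multiplicity rule are commonly left to an SAP, and their absence alone would be no finding. But this protocol does fix a list of methods, and all of those with a stated target are aimed elsewhere. It also fixes four HbA1c comparisons at a flat 5% and a cohort that excludes patients lost to follow-up. An SAP that followed the text would inherit these features.

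**A stronger reading: the independent-sample tests will be applied to pre/post data.** A reader might infer this and conclude that intervals would be too wide, power lost and Pearson's chi-squared misused on paired categories. The text does not support it. The sentence ties those tests to clinical groups, where they are suitable, and never applies them to change from baseline. That reading would also conflict with the multiplicity figure above, which presupposes valid paired tests.

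**A stronger reading: the Kolmogorov-Smirnov test decides which test is used.** Section 4.9 says only that it checks normality, directly after the choice between mean and median summaries. Its use as a gate is inference, so no defect is claimed.

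**A stronger reading: success on any of eight comparisons.** Four visits are fixed for HbA1c only, and the study calls itself observational and states no success rule. The grounded figure is about 16%.

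**Month 12 and the model are preferences.** In part this stands. The protocol names no primary visit, and month 12 is proposed because the programme lasts 12 months. With complete data a paired t-test would serve as well. The case for the model rests on keeping participants with missing visits.

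**Conclusion.** The point holds. Sections 2.1, 2.2 and 3.1 ask about within-patient change, and section 4.9 supplies no method for it. With valid paired tests, the four HbA1c comparisons at 5% carry about a 16% chance of at least one false positive; adding TIR raises this, to 25–29% only if TIR is tested at every visit too. Restricting the cohort under section 4.2 can produce a false fall of about 0.17–0.28 points when 25–30% drop out in relation to worse observed HbA1c.

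The dropout and power figures rest on an assumed SD of 1.5 and assumed correlations, and the dropout figures also on an assumed dropout mechanism. The protocol gives none of these. The multiplicity figure depends little on the correlation chosen.

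Two limits remain after any repair. Because entry requires HbA1c of 7% or higher, regression to the mean alone gives an apparent fall of 0.18–0.45 points at r = 0.8 to 0.5 (assumed population mean 7.5, SD 1.5), and no repeated-measures model removes it. Nor does the model replace a control group.

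**What to change.** 1. **HbA1c.** In section 4.9, specify one linear mixed model for repeated measures: visit as a five-level factor, unstructured within-patient covariance, age and sex as covariates, fitted to all enrolled participants with a baseline value. State the missing-at-random assumption.
2. **Cohort.** Amend section 4.2 so that loss to follow-up does not remove a participant; data collected up to that point stay in. Refusal to share data can remain an exclusion.
3. **Primary contrast.** Name one. Month 12 minus baseline fits the 12-month programme. Report months 3, 6 and 9 with confidence intervals only.
4. **Two primary outcomes.** State how the 5% is split or ordered between HbA1c and TIR, and whether tests are two-sided.
5. **TIR.** Use a similar within-patient analysis, with a method or robust standard errors suited to an outcome bounded at 0 and 100%.
6. **Group tests.** Keep the t-test, Wilcoxon and chi-squared tests for Group I versus Group II.

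The cost is a text amendment to sections 4.2 and 4.9, with no added visits or measurements; the model runs in R. The price is no significance claims at months 3, 6 and 9, and a ranking or alpha split between two outcomes that the protocol now leaves unranked. The power gain over a paired t-test is nil with complete data and about 2 to 7 points with 20–30% dropout, so the main benefits are a single prespecified test and protection against completer bias.
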